### Randomization and allocation concealment

2.7

Participants eligible for inclusion will be randomly assigned to three groups: the conventional treatment group, the moxibustion 15-min group, and the moxibustion 30-min group. An impartial administrator, not engaged in other study operations, will carry out this process, and the details of the random allocation list will remain absolutely confidential. The random allocation sequence will be computer-generated with a 1:1:1 ratio using the Electronic Data Capture System of Zhejiang Chinese Medical University.

### Blinding

2.8

This study will not employ blinding for administrators and patients across different moxibustion groups due to the particular characteristics of moxibustion manipulation. However, this study will be blind to the group assignment of outcome assessors made by a specifically designated person.

### Intervention procedures

2.9

All recruited patients will receive diabetes mellitus education tailored to their conditions and will manage their blood glucose levels through diet, exercise, oral hypoglycemic agents, and insulin administration. Patients with combined hypertension and hyperlipidemia will receive daily treatments aimed at lowering blood pressure and blood lipids, tailored to their specific conditions, to maintain normal control. The choice of medication will be based on the current medications the patients are independently using. The selection of medication must be determined by the patient’s existing self-medication practices.

#### Conventional treatment group

2.9.1

Mecobalamin tablets (0.5 mg/dose, 3 times/day) and epalrestat (0.5 g/dose, 3 times/day) will be administered orally for 4 weeks in conjunction with the patient’s daily treatment (basal medication treatment for patients with combined hypertension and hyperlipidemia).

#### Moxibustion groups

2.9.2

Both moxibustion groups will receive the same conventional treatment (mecobalamin and epalrestat) as the control group, with moxibustion as an add-on therapy. In the 15-min moxibustion group, the selection of acupoints is based on traditional Chinese medicine literature (28), moxa cones will be pasted on the acupoints, and moxibustion will be applied by ignition, each time for 15 min at each acupoint, once every three days, twice a week, four consecutive weeks of treatment. To ensure standardization, the moxa cone will be kept at a distance from the skin that elicits a warm sensation without causing pain or burning, and this distance will be consistently maintained by the practitioner.

The 30-min moxibustion group will follow the same operation as the 15-min moxibustion group apart from the intervention duration.

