### Diagnosis criteria

2.3

The diagnostic criteria for DPN, established in accordance with Chinese recommendations (27), are delineated as follows.

A clear history of Type 2 diabetes mellitus.Peripheral neuropathy that appeared at the time of or after the diagnosis of diabetes mellitus.Clinical symptoms (pain, numbness, sensory abnormalities, etc.) and signs are consistent with the presentation of DPN.Abnormalities in any of the 5 tests (ankle reflex, pinprick nociception, vibration sensation, pressure sensation, temperature sensation).Or in the absence of clinical symptoms, any two of the 5 tests are abnormal.Rule out other diseases that cause peripheral neuropathy. Identify neurotoxic effects caused by drugs, especially chemotherapeutic drugs, and neurological damage caused by metabolic poisons due to renal insufficiency.

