### Exclusion criteria

2.5

Those with peripheral neuropathy, ulcers, and gangrene of the limbs caused by various other reasons (e.g., hypothyroidism, alcohol, drugs, heredity, etc.), or those with a history of skin ulcers or lesions that do not heal easily.Women who are in preparation for pregnancy, during pregnancy, or breastfeeding.Those with acute complications such as combined diabetic ketoacidosis, lactic acidosis, severe infections, etc.Those who suffer from serious liver or kidney damage or serious cardiovascular and cerebrovascular diseases (angina pectoris, myocardial infarction, multiple cerebral infarctions, cerebral hemorrhage, etc.).Those who have scars or pigmentation on the skin of the testing site, will affect the accuracy of the test.Those who are participating in other acupuncture or drug clinical trials.

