## Discussion

3

As a consequence of the high prevalence of diabetes, DPN is a condition that not only places a load on individuals in terms of their mental burden and financial burden, but it also places weight on society. Most studies focus on acupuncture and electroacupuncture for the treatment of diabetic peripheral neuralgia in both clinical and basic research (16, 30–34), and there is a paucity of research on moxibustion. However, the use of moxibustion in the treatment of diabetic peripheral vascular disease is generally acknowledged in China, and impressive results have been achieved (35). The mechanism of moxibustion in treating DPN may involve the inhibition of NF-kappa B protein and mRNA expression, alongside the induction of Nrf2 protein and mRNA expression in the sciatic nerve, thereby restoring the balance between NF-kappa B and Nrf2 in rats with DPN (36). Moxibustion, although there is a scarcity of clinical studies owing to its operational instability, shows considerable effectiveness in the treatment of diabetic peripheral neuropathy. Therefore, offering a protocol for moxibustion treatment is significant.

Moxibustion, a highly regarded intervention for diabetic complications in China, enjoys popularity, particularly in the fields of rehabilitation and physiotherapy. As of now, the duration of moxibustion for addressing diabetic neuropathic pain remains uncertain and lacks a suitable and standardized protocol. Due to the operation of moxibustion’s lack of standardization, adverse events come and will bring varying degrees of impact on the health of patients such as necrotizing fasciitis (37). The phenomenon described, which pertains to accidents occurring during the moxibustion process, is relatively common. Conditions such as empyrosis, infection, and allergy may arise during surgery due to the prolonged hypoesthesia experienced by diabetic patients, particularly regarding a reduced sense of temperature (38, 39). In this case, it is essential to establish a clinical standard for moxibustion.

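### The stated limit on moxibustion heat relies mainly on what the patient feels, although patients with reduced temperature or pain sense are eligible; the delivery method is also unclear

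*Protocol article*

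**What the plan says.** Section 2.9.2 (Moxibustion groups) limits heat as follows: "To ensure standardization, the moxa cone will be kept at a distance from the skin that elicits a warm sensation without causing pain or burning". It adds that "this distance will be consistently maintained by the practitioner". The 30-min arm works under the same rule: "The 30-min moxibustion group will follow the same operation as the 15-min moxibustion group apart from the intervention duration".

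The same section describes delivery this way: "moxa cones will be pasted on the acupoints, and moxibustion will be applied by ignition, each time for 15 min at each acupoint".

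On who is treated, section 2.3 (Diagnosis criteria) counts "Abnormalities in any of the 5 tests (ankle reflex, pinprick nociception, vibration sensation, pressure sensation, temperature sensation". Section 2.4 admits patients with sensory abnormalities in the limbs. The nearest exclusion in section 2.5 covers "those with a history of skin ulcers or lesions that do not heal easily"; it does not mention reduced heat or pain sense.

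On the hazard, the Discussion states: "Conditions such as empyrosis, infection, and allergy may arise during surgery due to the prolonged hypoesthesia experienced by diabetic patients", and continues "particularly regarding a reduced sense of temperature". The surrounding text is about accidents during moxibustion, so I read the procedure meant there as moxibustion.

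**The concern.** A heat limit that depends on feeling warmth and pain protects a patient who feels both normally. A patient who feels heat poorly may report only mild warmth, or nothing, at a distance that injures the skin. The practitioner may even be led to move the cone closer to obtain the required warm sensation. This trial recruits from a population in which such loss is part of the disease, and its authors describe the resulting burns themselves.

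What is at stake is avoidable skin injury, with the longer exposure in the 30-min arm. A second, smaller matter is that a reader cannot tell from section 2.9.2 how the heat was applied. That matters for a trial whose stated purpose is to standardise moxibustion.

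**Working it through.** There is no figure in the plan to reproduce. The check sets the sections side by side, with one piece of arithmetic on exposure.

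**1. What the rule depends on.** Section 2.9.2 names three signals: warmth, pain and burning. Warmth and pain are reported by the patient. Burning can mean a felt sensation, which is again the patient's report, or damage to the skin, which the practitioner could see. On the second reading the signal may come only once injury has begun. The text gives no gap, skin temperature or skin check as a further limit.

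**2. Who can be enrolled.** Section 2.3 lists five tests, two of which are pinprick nociception and temperature sensation. With symptoms, one abnormal test is enough; without symptoms, two are needed. Ankle reflex and vibration sense are also on the list, and section 2.4 names both. A patient can therefore qualify with normal temperature and pinprick sense. The correct statement is that some enrolled patients may have reduced heat or pain sense, not that all will. Nothing in section 2.5 removes those who do.

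**3. Where the heat is applied.** Section 2.9.3 and Table 2 give ST36 (below the knee), SP6 (above the ankle), LI4 (hand) and LI11 (elbow). The Introduction places the main symptoms in the distal feet and toes, and section 2.3 does not say where on the body the tests are done. Sensory loss at the four treated points is therefore possible but not documented.

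**4. What else could catch a problem.** Section 2.6 allows withdrawal on a physician's judgement after adverse events or significant physiological changes. Section 2.10.5 has safety assessed at each session and lets clinicians decide on discontinuation. Both can limit repeat exposure. Neither sets a limit while the cone is burning.

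**5. Exposure under the rule.** Inputs from section 2.9.2: twice a week, 4 weeks, 15 or 30 min per point.
- Sessions: 2 × 4 = 8.
- 15-min arm: 8 × 15 = 120 min per point.
- 30-min arm: 8 × 30 = 240 min per point.

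**6. Delivery.** A cone pasted on the acupoint sits at the skin. A cone at a distance kept by the practitioner does not. Both descriptions hold if the cone sits in an adhesive holder that leaves a gap and that the practitioner can adjust or lift. The article describes no such holder.

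**The case against.** The strongest case against is that this is a condensed article. Gap size, type of holder, inspection interval and stopping signs belong in a standard operating procedure. Section 2.10.6 promises one, together with common training and monthly inspections. That stands for the missing details, and their absence is not the point. The point is the rule that section 2.9.2 does state, and presents as its means of standardisation: it can fail when followed exactly in patients whom the Discussion describes.

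Three further objections also carry weight.
- Sensory loss may lie mainly in the feet, away from the treated points. This limits what can be said about size. It does not remove the concern, because the rule makes no provision for a patient in whom the loss does reach a treated point.
- The practitioner attends throughout and may notice early redness. That is likely in good practice, but the text does not ask for it.
- The doubled exposure in the 30-min arm is the factor under test and not a fault. That is right; it is a reason to have a sound heat limit in both arms.

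A reader might also infer that the two descriptions of delivery contradict each other, so that no operating procedure could satisfy both, or that the three hospitals will deliver different treatments. The documents do not support either inference. A stick-on holder with a gap would satisfy both descriptions, and common training is planned. The wording is unclear, not impossible to follow.

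**Conclusion.** The point holds as a safety matter in how the intervention is specified. The stated heat limit relies mainly on patient sensation, people with reduced temperature or pinprick sense are eligible, and the Discussion ties burns to that deficit. In some patients the rule may therefore give late or no warning, over 120 or 240 min of heating per point. Separately, the delivery wording needs one clarifying statement.

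The size of the harm cannot be given: the documents state neither the share of patients with sensory loss at the treated points nor a burn rate. The conclusion assumes that at least some participants have such loss at a treated point, and that no unseen procedure already overrides the sensation rule.

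Two stronger readings should be resisted. One is that safety is unmonitored; sections 2.6 and 2.10.5 do provide for it, though only after an event or at session level. The other is that the comparison of 15 with 30 min is invalid; both arms work under one rule, and nothing here biases that randomised contrast. The change should be made, but no statistical figure in the plan depends on it.

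**What to change.** Amend section 2.9.2 in two respects.

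1. State one delivery method for both moxibustion arms, for example a stick-on holder with a fixed gap.
2. Add that reported sensation is not the sole heat limit. In both arms the practitioner inspects the skin at set intervals; widens the gap or stops at marked redness, blistering or any pain; and records the minutes given. The gap is never narrowed because a patient with reduced temperature or pinprick sense reports too little warmth.

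The last rule needs the temperature and pinprick results of section 2.3 to be available to the practitioner for each moxibustion patient, preferably tested beside the treated points.

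The cost is a text amendment, two brief bedside tests where they have not been done, and closer attendance by a practitioner who already has to maintain the distance. The interval is for the trial team to choose. If it were 5 min (an assumption, for scale only), there would be 15/5 = 3 inspections per 15-min application and 30/5 = 6 per 30-min application.

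The downside is that some applications will be cut short, possibly more often in the 30-min arm, which would reduce the contrast in minutes received. Recording the minutes given lets that be reported. If patients have already been treated, the date of the change should be recorded.

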#### Acupoint selection

2.9.3

Based on traditional Chinese medicine literature (28) and clinical experience, a prescription was developed for the following acupoints, adhering to the concepts of local and distal point selection: Zusanli (ST36), Sanyinjiao (SP06), Hegu (LI4), Quchi (LI11). The above acupoints will be on the affected side. The locations of the above acupoints are summarized in Table 2.

**Table 2 tab2:** Locations of the selected acupoints for diabetic peripheral neuropathy treatment.

Acupoint	Location
Zusanli (ST36)	3 cun below the patella, one fingerbreadth lateral to the anterior border of the tibia
Sanyinjiao (SP6)	3 cun above the medial malleolus, on the posterior border of the medial aspect of tibia
Hegu (LI4)	On the dorsum of the hand, between 1st and 2nd metacarpal bones, in the middle of the 2nd metacarpal bone on the radial
Quchi (LI11)	When elbow is flexed with the angle of 90°, the point is at the midpoint of the lateral end of the transverse cubital crease and the lateral epicondyle of the humerus

#### Concomitant care and intervention

2.9.4

During the study period, participants must avoid other DPN interventions, including behavioral therapies and medications, that could influence the study’s outcomes. Participants will be excluded if they receive additional combined interventions for the treatment of DPN. Participants with comorbid conditions, including hypertension, diabetes, and other chronic diseases, may maintain their standard medications and therapies. Research personnel will document the names of comorbid conditions, medications, and therapies in the case report form.

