### Withdrawal criteria

2.6

If adverse drug reactions, acupuncture-related adverse events, significant physiological changes, or severe complications or deterioration of the condition arise during the research process, and a professional physician evaluates that continued participation is inadvisable, the researcher must terminate the study.The patient is noncompliant and refuses to adhere to the therapy regimen.Participant voluntarily requests to withdraw.

Researchers must diligently record the rationale and timing of individuals’ removal from the trial. Individuals who have undergone more than half of the treatment regimen (≥4 sessions) should be incorporated into the efficacy analysis.

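### Section 2.9.4 excludes participants who take other DPN treatment during the study; if that means exclusion from the analysis, it is an outcome-related exclusion after randomisation in a trial whose patients know their arm

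*Protocol article*

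**What the plan says.** All references are to the protocol article.

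- **Section 2.9.4 (Concomitant care and intervention)** sets the ban: "During the study period, participants must avoid other DPN interventions, including behavioral therapies and medications". The consequence follows: "Participants will be excluded if they receive additional combined interventions for the treatment of DPN". The same section adds: "Research personnel will document the names of comorbid conditions, medications, and therapies in the case report form".
- **Section 2.5 (Exclusion criteria)** has one item on concurrent treatment, and it concerns other trials: "Those who are participating in other acupuncture or drug clinical trials".
- **Section 2.6 (Withdrawal criteria)** keeps some removed patients: "Individuals who have undergone more than half of the treatment regimen (≥4 sessions) should be incorporated into the efficacy analysis".
- **Section 2.9.1 (Conventional treatment group)** gives controls tablets only, which "will be administered orally for 4 weeks in conjunction with the patient"'s usual daily treatment. Section 2.9.2 gives the moxibustion groups the same tablets plus two sessions a week for 4 weeks, 8 in all.
- **Section 2.8 (Blinding)** says: "This study will not employ blinding for administrators and patients across different moxibustion groups". It then says that "this study will be blind to the group assignment of outcome assessors", which I read as blinded outcome assessors.
- **Section 2.10.1 (Primary outcome)** divides cured plus effective cases by the total number of cases, at week 4 and month 1. It does not define that total as all randomised patients.
- **Section 2.10.3 (Statistical analysis)** plans multiple imputation for the primary outcome.

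**The concern.** The exclusion sentence stands under intervention procedures and follows a ban that runs through the study period. It therefore reads as a rule that acts after allocation, and sections 2.4 and 2.5 contain no matching rule at screening.

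A patient who seeks further DPN treatment has probably had too little relief. Excluding such patients from the analysis would tend to remove ineffective cases. Two features could make the removal unequal between arms. Controls know that they are not receiving moxibustion and may look elsewhere more often. Moxibustion patients are seen at 8 sessions, so their use may be noticed more often. These pull in opposite directions, and the article does not show which is stronger. Either way, the comparison would no longer rest on randomisation alone.

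**Working it through.** **Inputs.** From section 2.10.4: control rate 60%, moxibustion rate 90%, two-sided alpha 0.05, 30 randomised per arm. The number excluded is not given, so every exclusion figure below is an assumption. All cases take exclusion to mean exclusion from the analysis.

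**The plan's own figure.** There is no stated figure for exclusions. The 30 per arm follows from 24/(1 − 0.20) = 30. The 24 does not follow from the stated inputs: [1.960·√(2·0.75·0.25) + 1.282·√(0.6·0.4 + 0.9·0.1)]²/0.30² = 41.7, so 42 per group. That is a separate matter. It explains why the baseline power below, at 30 per arm with nobody lost, is 80% and not 90%.

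**Effect on the observed rate.** With true rate p, share q of failures excluded and share r of responders excluded:

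rate read = p(1 − r) / [p(1 − r) + (1 − p)(1 − q)]

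A control arm of 30 at 60% has 18 responders and 12 failures.

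- 2 failures excluded: 18/28 = 64.3%
- 4 failures excluded: 18/26 = 69.2%
- 4 failures and 2 responders excluded: 16/24 = 66.7%
- equal shares of both (q = r): 60%, no bias

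**Effect on the test.** Pearson chi-square without continuity correction, control against one moxibustion arm. Each failure is excluded independently with probability q. The rejection probabilities come from enumerating all outcomes.

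| Failures excluded (share q) | Power, 60% vs 90% | Type I error, 60% vs 60% | in favour of moxibustion | in favour of control |
|---|---|---|---|---|
| none | 80% | 4.9% | 2.4% | 2.4% |
| control 1/6 (2 of 12) | 68% | 6.5% | 1.1% | 5.4% |
| control 1/3 (4 of 12) | 51% | 11.2% | 0.4% | 10.8% |
| control 1/3, moxibustion 1/6 | 58% | 6.8% | 1.0% | 5.8% |
| 1/3 in both arms | 66% | 5.2% | 2.6% | 2.6% |
| moxibustion 1/3 only | – | 11.2% | 10.8% | 0.4% |

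Control-only removal therefore makes a false claim for moxibustion less likely. That claim becomes more likely only when a moxibustion arm loses more failures.

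**Does section 2.6 prevent this?** If it governs these exclusions, a moxibustion patient with at least 4 of 8 sessions stays in. Controls have no sessions to count, so a control with the same history has no stated route back.

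**Does imputation prevent this?** Section 2.10.3 does not say that it covers those excluded under 2.9.4. If it did, and imputed from retained patients by arm alone, the 4 excluded controls would be filled in at 69.2%: (18 + 4 × 0.692)/30 = 69.2%, the same biased value. A baseline predictor would recover only part of the gap, because the exclusion depends on the outcome itself.

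**The case against.** The strongest reply is that section 2.9.4 never says what participants are excluded from. It may mean only that study treatment stops. Section 2.6 is the one place that deals with analysing removed patients. Taking a banned treatment can fairly be read as the noncompliance listed there, in which case patients with enough sessions stay in. This stands as a matter of reading. A reader might infer that the plan certainly drops these patients, or that 2.6 and 2.9.4 contradict each other; the text supports neither. What remains is that the 2.6 route is defined only for patients who have sessions.

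Analysis sets and imputation models are commonly left to an analysis plan that is not shown here. That is accepted, and their absence is not the point. The point is the one consequence that 2.9.4 does state.

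The size is wholly assumed. The window is 4 weeks plus one month, and all patients receive two drugs for DPN. Losing 6 failures from one arm would use up its entire 20% dropout allowance (0.20 × 30 = 6), so the illustrations stop at 4. A reader might also infer that the rule inflates the evidence for moxibustion. The documents do not support that: if controls seek other treatment more often, the bias runs against moxibustion.

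Finally, keeping these patients has a statistical price, because outside treatment can then alter the contrast. This stands and is set out under the fix.

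**Conclusion.** The sentence should be changed. As written, it permits an exclusion after randomisation on an event probably related to outcome, with unblinded patients and only an unequal safeguard. Nothing in the article shows that harm will occur. The exclusion rate is unknown, the direction is open, and the net bias may be zero. If equal shares of failures leave both arms, type I error stays near 5%, although power still falls (66% in the case shown).

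Under the assumed loss of 2 or 4 of 12 control failures from the analysis, the control rate is overstated by 4 or 9 percentage points and power drops by about 12 or 29 points. The accompanying rise in type I error mostly favours conventional treatment. Confidence is medium, because the conclusion depends on reading the exclusion as applying to the analysis and on extra treatment being linked to poor response.

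**What to change.** Keep the ban in section 2.9.4 and replace the exclusion sentence with: *Other DPN treatment taken after randomisation is recorded with its start date; the participant is still assessed at week 4 and month 1 and is analysed in the arm as randomised.*

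Use the observed grade from the blinded assessor in the primary analysis, because an unblinded patient's decision to seek treatment does not by itself set it. In a sensitivity analysis, count users of other DPN treatment as ineffective. Put any screening rule on other DPN treatment in section 2.5, applied before randomisation.

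**Cost.** A few sentences and one start date on a case report form that already documents medications and therapies. There are no extra patients, and both visits are already scheduled.

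The change is not free statistically. The observed grade absorbs any effect of outside treatment. If 1 or 2 of 4 control users become effective cases, control reads 19/30 = 63.3% or 20/30 = 66.7%, and power against 90% is 71% or 61%, compared with 80%. If 3 of the 4 convert, control reads 21/30 = 70%, slightly further from 60% than the 69.2% from excluding them. The difference is that the result then answers a defined question, the effect of assignment with outside treatment as it occurred, and randomisation is preserved.

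Counting users as ineffective errs the other way. If 3 of 18 control responders also use other treatment and no moxibustion patient does, control reads 15/30 = 50%, and with no true difference type I error is about 12%. That is why it belongs in the sensitivity analysis.
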